## Abstract

**Background**: Based on the available evidence, there are no published clinical trials that have analyzed the effectiveness of adding cross-education, mirror therapy, and virtual reality exercises (combined) to standard treatment to improve clinical outcomes in patients after anterior cruciate ligament (ACL) reconstruction. **Methods**: A total of 58 patients with ACL reconstruction, aged 18–50 years, will be randomized (1:1) to two treatment arms. The control group (n = 29) will receive a standard physiotherapy program based on a consensus developed by the Sport and Health Rehabilitation Guidelines. The experimental group (n = 29) will receive a novel physiotherapy program that includes cross-education exercise with visual biofeedback, mirror therapy, and virtual reality in addition to the standard exercise program. Five evaluations will be performed: at the beginning of physiotherapy treatment (baseline), at 6 weeks, 12 weeks, 24 weeks and 52 weeks after surgery. The primary outcome will be passive knee extension range of motion at 6 weeks (for sample size), assessed by goniometry; the remaining outcomes are secondary and exploratory. The secondary outcomes measures will be pain intensity, fear of movement, the level of anxiety, knee function, and isometric quadriceps strength. **Discussion**: We hypothesize that patients who receive a novel physiotherapy program that includes cross-education with visual biofeedback, mirror therapy, and virtual reality will show greater benefits in knee extension and other clinical outcomes than those who receive a standard physiotherapy program. **Conclusions**: The trial proposed in this protocol will provide new data on the effectiveness of the combination of cross-education, motor imagery, and virtual reality therapy added to a standard physiotherapy program compared with the standard physiotherapy program alone in patients who undergo ACL reconstruction. The findings will generate new insights into the effects of the interventions and expand the multimodal rehabilitation strategies available to patients who undergo this surgery.

## 1. Introduction

Anterior cruciate ligament (ACL) injury is a health problem that generates significant costs in a person’s years of productive life. In the United States, approximately 200,000 ACL injuries occur each year, and an estimated 400,000 ACL reconstructions are now performed annually and generating expenses to the health system between US$625 million and US$1 billion annually [1,2,3]. This volume reflects a sustained upward trend: over a 17-year period, the age-standardized incidence of primary ACL reconstruction rose by roughly 26% (from 40.6 to 51.2 per 100,000 people aged ≥10 years), with the increase being most pronounced among women [3]. Based on epidemiological studies, after 2 years of follow-up, there is a high risk of re-tear after ACL surgery. This risk increases exponentially to 25 times more when physiotherapeutic treatment fails in the early stages [4,5]. Evidence shows that these injury risks after ACL reconstruction are because patients who undergo surgery show quadriceps weakness, abnormal movement patterns, and low neuromuscular activity [6,7]. Moreover, in early stages, a lack of knee extension is the most prevalent deficit in this clinical condition, which has been associated with poor knee function and low long-term quadriceps muscle strength [8]. Likewise, other studies have shown that persistent quadriceps weakness and a lack of knee extension contributes to knee instability, disability, risk of knee osteoarthritis, and increased re-injury rates at 2 years after surgery [9,10].

Previous evidence has attempted to explain how this clinical impairment could generate neurophysiological maladaptations after ACL injury [11,12]. Kapreli et al. [11]. demonstrated that patients with ACL injury have low activation in sensorimotor cortical areas assessed with functional magnetic resonance. Diekfuss et al. [12] showed that patients with ACL reconstruction have a stronger functional connection between a cortical sensory-motor region and a cerebellar region responsible for balance and coordination in the lower limb. Other studies have demonstrated that patients with ACL reconstruction show an increased motor threshold and low excitability of the motor cortex, generating a deficient “output” of descending motor neurons toward the muscles of the lower extremity [13,14,15,16]. Therefore, patients with ACL tears may have a greater motor planning demand to generate optimal movement and better function of the lower extremity. Additionally, other clinical changes are related to a greater fear of movement of re-injury and pain intensity during ACL reconstruction rehabilitation [17]. In the same way, these clinical manifestations—including fear of movement and anxiety associated with aspects related to pain—are caused by the increased neural activity of mesolimbic areas and the amygdala [11,17].

The current approach of physiotherapy after ACL surgery focuses on improving the functional impairment of the clinical condition and preventing a re-injury: improving early range of motion (ROM), increasing the quadriceps muscle strength, and achieving a good functional gait and knee function [18]. However, studies that have analyzed the effect of conventional physiotherapy protocols have reported a lack of knee extension, decreased activation of the quadriceps, gait asymmetry, and a greater probability of re-tear up to 2 years after reconstruction surgery [19,20]. Therefore, the appropriate early physiotherapy program for patients who undergo ACL surgery remains a topic of debate in the literature. There is recent evidence that graded motor imagery (GMI), cross-education exercises, and virtual reality are therapeutic tools that attempt to facilitate neuromuscular activation as well as sensory reorganization of the cerebral cortex, and to improve functional outcomes [21,22]. 

GMI includes three stages: recognizing judgments of laterality, movement imagery, and mirror therapy. Mirror therapy effectively improves motor cortex activation and decreases the neural activity of pain-processing areas [23]. Additionally, mirror therapy activates the premotor cortex and supplementary motor area to increase motor neuron function to the peripheral muscle [24]. Cross-education refers to strength gain observed in the contralateral limb after a unilateral training program [25]. A meta-analysis reported that quadriceps muscle strength can be increased by up to 18% by working the contralateral limb [26]. Moreover, applying motor activation and visual strategies for the limb contralateral to the affected limb improves information processing at the cortical level, reducing pain perception and increasing contralateral muscle strength [25,27]. Finally, another systematic review, conducted in patients with knee osteoarthritis, specifically indicated that virtual reality improves functional outcomes of the lower limb [28]. Therefore, implementation of these strategies from the early stages of a standard physiotherapy program may ameliorate changes in cortical reorganization and thus improve muscle activation and prevent a re-tear in these patients. Recent evidence supports the use of cross-education in this population: in a randomized controlled trial, adding contralateral cross-education training to conventional rehabilitation after ACL reconstruction produced greater improvements in knee function, kinematic parameters, dynamic balance, and plantar pressure than conventional rehabilitation alone [29]. However, that trial evaluated cross-education in isolation, and did not combine it with visual biofeedback, mirror therapy, or virtual reality. Therefore, to our knowledge, no published clinical trial has analyzed the effectiveness of adding cross-education alongside visual biofeedback, mirror therapy, and virtual reality exercises to standard treatment. We hypothesize that, compared with standard physiotherapy alone, patients allocated to the novel physiotherapy program (multimodal intervention) rather than to standard treatment will show a significantly greater improvement in passive knee extension range of motion at the 6-week primary endpoint. Finally, the aim of this study is to describe the rationale and methods of a randomized clinical trial that will assess the effectiveness of a multimodal intervention that includes cross-education alongside visual biofeedback, mirror therapy, and virtual reality exercises added to standard treatment to improve clinical outcomes in patients who undergo ACL surgery.

## 2. Materials and Methods

### 2.1. Study Design/Setting

This will be a single-blind, two-arm, parallel-group superiority randomized controlled trial, designed to assess the effectiveness of the addition of a novel multimodal physiotherapy program to standard treatment, which is superior to standard treatment alone for passive knee extension in patients undergoing ACL reconstruction. It will be conducted at the Physical Therapy Department of the Chilean Medical Center. This protocol is based on Standard Protocol Items: Recommendations for Interventional Trials (SPIRIT) guidelines, and the checklist is available in the Supplementary Materials [30]. The participants are residents who will mainly be recruited in the city of Santiago. The participants will be informed about the research, procedures, risks, and benefits by [name]. If they agree, then they will sign an informed consent form. Only those participants who read and agree to the protocol and who sign the informed consent form will be part of the study, following the schedule described in Figure 1.

### 2.2. Participants

This study will include 58 patients of the Private Clinical of Chile who undergo ACL reconstruction (patellar bone–tendon–bone, gracilis semitendinosus tendon, and/or allograft). All patients will be treated with postoperative relative rest for 4 days and will be prescribed an oral nonsteroidal anti-inflammatory drug twice a day for 14 days depending on the context of each patient. The patient will be referred to the Physical Therapy Department 2 weeks after surgery.

#### 2.2.1. Inclusion Criteria

To participate in this study, the participants will have to meet the following inclusion criteria: (1) men and women aged 18–50 years with an ACL reconstruction, who have undergone an independent reconstruction surgery of the ACL (with or without other injuries such as a meniscus tear with a meniscal suture, collateral ligament injury, posterior ligament sprain, etc.) with a normal body mass index (18.50–24.99 kg/m^2^); (2) agreement to participate in the trial and signing the informed consent form; and (3) the ability to follow simple orders in Spanish (based on a Mini-Mental State Test score >26 points).

#### 2.2.2. Exclusion Criteria

Patients will be excluded if they meet any of the following criteria: (1) unable to walk after surgery; (2) other pathologies associated with the knee joint including knee osteoarthritis, degenerative injuries, or patellar tendinopathy prior to surgery, posterior cruciate ligament injury, and re-tear of the ACL; (3) orthotic devices in the knee joint; and (4) some degree of cognitive impairment.

### 2.3. Interventions

During the trial, all participants will receive the same standardized postoperative regimen (relative rest for four days and oral non-steroidal anti-inflammatory drugs twice daily for 14 days), with paracetamol permitted as rescue analgesia. The following co-interventions will not be permitted during the supervised treatment period: additional supervised physiotherapy outside the trial, intra-articular or peri-articular injections, additional structured strengthening or exercise programs, and routine prophylactic bracing beyond that prescribed by the operating surgeon. Any analgesic use, unsupervised exercise, bracing, or additional treatment will be recorded at each assessment in the eCRF and incorporated as a covariate in sensitivity analyses.

The control group (n = 29) will receive a standard physiotherapy program based on the consensus statement of the Sport and Health Rehabilitation Guidelines MOON Group [31]. This program proposes to control signs and symptoms for 2 weeks after surgery. The main components at this stage are to control edema, to reduce pain, to achieve a normal gait pattern, and to start muscle activation of the quadriceps; and to provide the participant with education about their clinical condition and evolution. In stage 1 (0–6 weeks), local cryotherapy will be performed for 15 min in addition to conventional transcutaneous electrical nerve stimulation (TENS at 120 Hz and 50 Us).

From 0 to 2 weeks, four exercises will be performed: (1) Basic therapeutic mobilization of knee extension in the prone position, knee flexion in the supine position, and patellar mobilization. (2) Isometric exercise of the quadriceps in the supine position with 10 s of isometry for 30 repetitions. (3) Hamstring exercise in the sitting position with the knee slightly in flexion (the participant will be asked to push their foot toward the floor for the contraction). (4) Hip abduction exercises in the side position. The participant will be asked to take off one knee from the other and maintain the position for 5 s for 30 repetitions.

From 2 to 6 weeks, six exercises will be performed: (1) Basic therapeutic mobilization of knee extension in the prone position. (2) Knee flexion in the supine position with the feet supported against a wall to increase the ROM. (3) Semi-squat with the back supported on the wall, with three series of 15 repetitions. (4) Step-up on both legs, with 20 repetitions per leg. (5) Bridge of one leg in extension, maintaining the position for 10 s. (6) Hamstring with a red elastic band, with three series of 20 repetitions. During this phase, aerobic exercise will be added (20 min on a cycle ergometer). Stage 2 (6–12 weeks) will involve complete knee ROM, dynamic knee exercises, painless control, small squats without pain and the “giving way” feeling, and knee flexion at 8 degrees without pain. Seven exercises will be performed: (1) Full squats in the protected range, with three series of 20 repetitions. (2) Leg press between 90 and 0 degrees according to a tolerable load, with three series of 12 repetitions. (3) Hamstring curl in press, with three series of 20 repetitions. At this stage, four dynamic control and balance exercises will be added. (4) Unipodal disturbance training. (5) Diagonal landslides on stable surfaces. (6) Jumps without pain on unstable surfaces. (7) Ball launch exercises to the wall with unstable surfaces, with the addition of a cognitive task, where there are three series of 20 repetitions. This phase will also include aerobic exercise (40 min on a cycle ergometer).

The specific components of stage 3 (12–24 weeks) include jumping without pain, and achieving daily and sports life activities without a sense of fear of movement or injury. The same exercises described in stage 2 will be performed, increasing the progressions and load (to 2 kg) according to the tolerance of each participant. In addition, four exercises will be added.

(1)Management and deceleration changes exercises with obstacles for 5 min.(2)Squats at 90 degrees, maintaining the position for 10 s for 30 repetitions.(3)Exercises on an unstable platform with cognitive tasks in a unipodal position.(4)Exercises for reintegration to sport activity according to the participant’s preference.

This phase will also incorporate aerobic exercise (50 min on a cycle ergometer). All sessions in stage 3 will last approximately 90 min. There will be three weekly sessions for 24 weeks.

The intervention group (n = 29) will receive a novel physiotherapy program that includes cross-education exercise with visual biofeedback, mirror therapy, and virtual reality in addition to the standard treatment based on the MOON group guidelines (as described above for the control group). This intervention also includes three stages. In stage 1 (0–6 weeks), cross-education exercises will be added to the first two weeks. The specific cross-education components are strength gain of the injured limb, training the contralateral side, increasing the excitability of corticospinal pathways, and reducing the inhibition of the motor cortex due to the injury. To perform cross-education with visual biofeedback, while in the supine position, the participant will be shown a video of an isometric contraction of quadriceps in real time on an electronic device (tablet). The participant will be asked to look at the video during each contraction and simultaneously perform an isometric contraction of the contralateral (non-operated) leg for 10 s, with 30 s of rest. This exercise will be performed for 15 min (Figure 2).

In stage 2 (2–6 weeks), the same exercises mentioned in stage 1 will be performed, increasing the progressions of isometry to 20 s, with 45 s of rest. In addition, mirror therapy exercises will be added. While the participant is sitting, a mirror will be installed between both limbs. The participant will be asked to perform knee-extension movements with the non-operated limb, which should simulate the injured limb. The participant will be asked to perform the movement for 10 min. These interventions will be performed at least two times a week. The specific components of mirror therapy are a decrease in the somatosensorial areas related to pain and activation of brain motor areas to increase neuromuscular activity without generating movement of the limb to avoid pain and muscle fatigue. In addition, during the last two weeks, virtual reality exercise will be performed using a lower-limb rehabilitation application (Corpus VR—InMotionVR, version to be specified at the time of publication, or the native application running on Oculus Meta Quest 3S). While seated, the participant will wear the virtual reality headset and perform a lower-limb virtual reality game consisting of fishing for different objects from a virtual lake (Figure 3), using active knee extension of the operated limb to reach and “catch” each target. The objective of the game is to sustain controlled, repeated active knee extension within a progressively increasing range of motion while maintaining task engagement through the gamified format. Progression will be criterion-based: as the participant demonstrates adequate control and a pain-free range of motion, the target distance and range of motion will be increased, session duration will progress from 15 to 30 min, and task complexity/speed will be increased as tolerated. This exercise will be performed for 30 min, twice per week. The specific components of virtual reality are an increase in neural activity in the motor and premotor cortices to improve connectivity in corticomotor pathways and to improve muscle activation. All sessions will last approximately 60 min. Cross-education exercises with visual biofeedback, mirror therapy, and virtual reality will be added to the standard therapy in each session for each participant. There will be three weekly sessions for 24 weeks.

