### 2.4. Outcome Measures

Participants will undergo five standardized assessments across the postoperative follow-up, scheduled at week 2 (baseline), week 6, week 12, week 24 (~6 months), and week 52 (12 months). The baseline assessment (week 2) will capture demographic variables and potential confounders together with the pre-intervention values of all efficacy outcomes, establishing the reference against which subsequent change is estimated. Outcomes are organized hierarchically. The single primary (confirmatory) outcome is the adjusted between-group difference in passive knee extension ROM at the 6-week postoperative assessment—the timepoint at which the intervention is hypothesized to exert its principal effect and the only outcome for which the trial is powered (Section 2.5). Passive knee extension ROM at the later assessments (24 weeks and 12 months) and all remaining efficacy outcomes—pain intensity (VAS), kinesiophobia (TSK-17), pain-related anxiety (PASS-20), knee function (KOOS), isometric quadriceps strength, and thigh circumference—are designated secondary and exploratory (hypothesis-generating). Re-tear and adverse events are safety outcomes. Two physiotherapists who are not part of the research team will perform the measurements. They will be blind to group assignments to avoid possible biases in the measurement.

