### 2.7. Randomization and Blinding

The participants will be randomly allocated to the two groups through a sequence of numbers generated by a computer program (1:1) before beginning the selection process. The group assigned to each participant will be kept in a sealed envelope so that only the researcher who makes the assignments will know to which group each participant belongs (Figure 4). Given the nature of the interventions, blinding physiotherapists and participants will not be possible. However, the assessors and statisticians will be blinded to which group the participants belong.

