Because the confirmatory hypothesis is tested through a single primary contrast (the adjusted between-group difference in passive knee extension ROM at 6 weeks), no adjustment for multiplicity is required for the primary analysis, and statistical significance for the primary outcome will be evaluated at a two-sided α = 0.05. All secondary and exploratory analyses—passive knee extension ROM at 24 weeks and 12 months and every secondary outcome—are exploratory and will not be subjected to formal multiplicity control; no secondary outcome is designated a key secondary endpoint for confirmatory testing, and no hierarchical or gatekeeping procedure is therefore applied. For these outcomes, we will report adjusted mean differences (or the corresponding effect measure) with 95% confidence intervals, interpreted as hypothesis-generating. We explicitly acknowledge that the family-wise type I error rate is not controlled across these comparisons, and we will refrain from confirmatory claims based on them. The primary estimator is the adjusted between-group difference in passive knee extension ROM at 6 weeks. This will be estimated by analysis of covariance (ANCOVA), with the 6-week passive knee extension value as the dependent variable, treatment group as the factor of interest, and baseline value of the outcome as a covariate, together with prespecified prognostic covariates; the treatment effect will be reported as an adjusted mean difference with its 95% confidence interval. The adjusted between-group difference at 6 weeks was chosen as the primary contrast in preference to a group-by-time interaction or a difference in change from baseline, because the primary endpoint is defined at a single timepoint, and ANCOVA adjusting for the baseline value is the more efficient and less biased estimator. The 6- and 12-month outcomes, and all secondary outcomes, will be analyzed using analogous baseline-adjusted models and are considered secondary. Partial eta squared (η^2^) will be reported as a measure of effect size (small 0.0–0.13, medium 0.13–0.26, large > 0.26). All primary and secondary outcomes will be analyzed following the intention-to-treat (ITT) principle, which is prespecified as the primary analysis strategy: every randomized participant will be included in the group to which they were allocated, irrespective of adherence, protocol deviations, or discontinuation of the allocated intervention. This strategy is fixed a priori and is not contingent on the observed pattern of missing data. Missing data will be assumed to be missing at random and handled using multiple imputations by chained equations (m = 50 imputed datasets) [42]. The imputation model will include the baseline value of the outcome, treatment allocation, age, sex, body mass index, graft type, and all post-baseline outcome measurements, with estimates pooled using Rubin’s rules. The robustness of the findings will be examined in prespecified sensitivity analyses, subordinate to the primary ITT analysis, comprising a complete-case analysis, a per-protocol analysis (participants achieving ≥ 80% adherence), and a pattern-mixture (tipping-point) analysis to test the sensitivity of the results to plausible departures from the missing-at-random assumption [42]. Analyses will be conducted in SPSS Statistics version 26 (IBM Corp., Armonk, NY, USA) and GraphPad Prism version 10.0 (GraphPad Software, San Diego, CA, USA).

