Cross-education has shown positive results in improving function and quadriceps and hamstring strength after ACL reconstruction [46]. However, the results differ depending on the time of evaluation and the variables assessed. These discrepancies may be due to differences in the planning of therapeutic exercises and the variables used for assessments. On the other hand, due to the common neurophysiological mechanisms of neural plasticity in the cerebral cortex, and the cognitive–affective mechanisms between motor imagery, virtual reality, and cross-education, the effects of these therapies could be enhanced when they are combined [47,48]. Some studies on post-surgery patients have shown positive effects of motor imagery combined with standard rehabilitation on pain intensity, kinesiophobia, and muscle strength [49,50]. Conversely, a previous systematic review provided no clear evidence that motor imagery is an effective intervention after ACL reconstruction [51]. The inconsistency of the results could be due to differences between with patients with osteoarthritis and ACL injury. Regarding the mechanisms in these clinical conditions, the pathophysiological mechanisms involved are different, which may influence the outcomes and responses of patients to interventions in the early stages [50,51]. The evidence for virtual reality therapy is consistent. Based on meta-analyses, it can be said that virtual reality therapy alone has positive effects that are superior to traditional therapy on functionality, strength, pain intensity and joint range [52]. The beneficial effects of this therapy are based on the fact that it facilitates cognitive distraction and attentional engagement, and redirects focus away from the perception of pain and fear of movement [52,53]. In addition, virtual reality activates neural pathways that allow for optimizing neuromuscular coordination and improve the proprioception of the lower limb [53]. Beyond virtual reality, other technology-assisted approaches have also been used to support functional rehabilitation. For example, mechatronic and robotic-assisted gait training systems have been developed to provide controlled, repetitive, task-specific movement patterns that facilitate neuromuscular re-education and motor relearning; a usability pilot study of one such mechatronic gait rehabilitation system reported good acceptance among patients and clinicians, supporting the feasibility of incorporating device-assisted training into rehabilitation protocols [54,55]. These assisted rehabilitation strategies, together with virtual reality and cross-education, illustrate the growing trend toward multimodal, technology-supported rehabilitation programs aimed at optimizing motor recovery after musculoskeletal and neurological injuries, including ACL reconstruction.

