## Figures and Tables

**Figure 1 jcm-15-05552-f001:**
[figure not shown]
SPIRIT schedule of enrolment, interventions, and assessments. Columns indicate the corresponding postoperative time for each timepoint (Week 2 at enrolment/allocation, Week 6, Week 12, Week 24 [~6 months], and Week 52 [12 months]); the shaded band denotes rehabilitation Stages 1–3 (Section 2.3); row colors distinguish the primary outcome (knee ROM), secondary/psychosocial outcomes, safety/adverse event monitoring, and enrolment/baseline data, as detailed in the legend beneath the table.

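### Co-interventions recorded after allocation are to be covariates in sensitivity analyses; if treatment changes them, the adjusted result is not a valid check of the ITT effect

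*Protocol article*

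**What the plan says.** Section 2.3 (Interventions) sets the rule: use of analgesics, exercise outside supervision, bracing and any extra treatment "will be recorded at each assessment in the eCRF and incorporated as a covariate in sensitivity analyses". It does not restrict the rule to values obtained before allocation.

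On timing, the Figure 1 legend gives the schedule as "Week 2 at enrolment/allocation, Week 6, Week 12, Week 24" (about 6 months) and week 52. On blinding, Section 2.7 states that "blinding physiotherapists and participants will not be possible".

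Section 3 (Statistical Analysis) defines the primary analysis as a 6-week ANCOVA on treatment group with the "baseline value of the outcome as a covariate, together with prespecified prognostic covariates". It fixes intention to treat as the primary strategy, regardless of adherence, deviations or discontinuation. Its prespecified sensitivity analyses are given as "comprising a complete-case analysis, a per-protocol analysis" and a pattern-mixture (tipping-point) analysis. A model adjusted for co-interventions is not among them.

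**The concern.** Covariate adjustment in a randomised comparison is safe for variables fixed before allocation. A variable measured afterwards may itself be a result of treatment. Holding it constant then removes whatever part of the effect passes through it. If it also shares unmeasured causes with the outcome, such as how well the knee is recovering, adjustment creates an association between arm and outcome that is not causal.

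At stake is how the sensitivity analyses are read. Their purpose in Section 3 is to test whether the ITT finding is robust. A model that targets a different quantity without saying so cannot show this: a gap from the primary result could be fragility or merely the change of target, and agreement could be coincidence.

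**Working it through.** **1. Are the covariates post-randomisation?** Allocation is at week 2 (Figure 1 legend). Records are made at each assessment: weeks 2, 6, 12, 24 and 52 (Section 2.4). Only the week-2 record can precede allocation. The record that would accompany the 6-week primary endpoint does not.

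**2. Can treatment plausibly change them?** The protocol supplies the links.
- Analgesic use: mirror therapy is described as lowering activity in pain-related brain areas (Sections 1 and 2.3), and the Discussion says that virtual reality "redirects focus away from the perception of pain and fear of movement". Less pain plausibly means less rescue analgesia.
- Unsupervised exercise: the limitations in the Discussion accept that engagement and motivation may be higher in the experimental arm.
- Bracing and additional treatment: the link is weaker. Section 2.3 bars outside supervised physiotherapy, injections, structured exercise programmes and bracing beyond the surgeon's prescription, so these should be uncommon.

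**3. The plan's own scale.** With 24 per group and d = 0.83, two-sample t-test power at two-sided 0.05 is 0.804, which reproduces the stated 80%. In degrees, 0.83 × 3 = 2.49 and 0.83 × 4 = 3.32, so the target at 24 per group is about 2.5–3.3°. This point does not dispute those figures.

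**4. Effect of adjusting (assumed values).** The documents give no figure for how treatment alters co-intervention use or how such use relates to extension. Let M be the co-intervention in SD units, and:
- a = effect of treatment on M (SD)
- b = effect of M on extension (degrees per SD)
- g, h = effects of an unmeasured recovery factor on M and on extension

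In a linear model with M's within-arm variance equal to 1:

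adjusted coefficient = total effect − a·b − a·g·h

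| Total effect | a | b | g | h | Formula | Simulated (400,000 subjects) |
|---|---|---|---|---|---|---|
| 3° | 0 | 1 | 0.5 | 1.5 | 3.00° | 2.99° |
| 3° | 0.5 | 1 | 0 | 0 | 2.50° | 2.48° |
| 3° | −0.5 | −1 | 0 | 0 | 2.50° | 2.51° |
| 3° | −0.5 | 0 | 0.5 | −1.5 | 2.625° | 2.64° |
| 3° | −0.5 | −1 | 0.5 | −1.5 | 2.125° | 2.13° |
| 0° | −0.5 | 0 | 0.5 | −1.5 | −0.375° | −0.38° |
| 0° | 0.5 | 1 | 0 | 0 | −0.50° | −0.51° |

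Without M, the group coefficient recovers the total effect in every row (2.99–3.02° for a true 3°, about 0° for a true 0°). For a true 3°, the loss where treatment affects M is (3 − 2.64)/3 = 12% to (3 − 2.13)/3 = 29%.

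The direction depends on signs that the protocol does not fix. If treatment lowers analgesic use (a = −0.5) but analgesia itself helps extension (b = 1, g = h = 0), the formula gives 3 + 0.5 = 3.5°, an overstatement.

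**5. A second illustration, also assumed.** If analgesic use at 6 weeks falls from 50% to 25% and users have 1–3° less extension, adjustment removes 0.25 × 1 = 0.25° to 0.25 × 3 = 0.75°. Relative to the target that is 0.25/3.32 = 8% to 0.75/2.49 = 30%.

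**6. Section 2.3 against Section 3.** Section 2.3 commits to a covariate-adjusted sensitivity analysis. Section 3 lists three prespecified sensitivity analyses, and this is not one of them.

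**The case against.** The strongest reply is that little depends on this. The rule is confined to sensitivity analyses, Section 3 subordinates its sensitivity analyses to the primary ITT analysis, and no power, alpha or decision rule uses it. That stands, and it limits the severity.

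Several stronger readings are tempting but unsupported:
- A reader might infer that the analysis is biased by construction. It is not: with a = 0 there is no bias, and several of the listed co-interventions are prohibited and should be rare. The argument is strongest for analgesic use and unsupervised exercise.
- A reader might infer that a null effect could readily be made to look real. Under the assumed shifts of 0.38–0.51°, with SD 3–4° and 24–29 per group, a two-sample t-test would reach p < 0.05 about 6–10% of the time against a nominal 5%. That is an inflation, but a modest one.
- A reader might take 8–30% as the expected loss. The scheduled anti-inflammatory course lasts 14 days and so ends about when participants enter. Nothing in the documents supports 50% against 25% use at week 6. The top figure pairs a 3° association, a full SD at the lower end of the plan's range, with the smallest target.
- A reader might say that Sections 2.3 and 3 contradict each other. Section 3 leaves the analysis off its list; it does not forbid it.

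It can also be said that model details belong in an SAP. This point does not rest on missing detail: the protocol states a rule, and nothing confines that rule to safe values.

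**Conclusion.** The point holds in limited form. As worded, the rule admits post-randomisation values as ordinary covariates in an open-label trial whose rationale makes at least two of them plausible effects of treatment. If treatment does affect them, the adjusted coefficient does not estimate the ITT effect and is not a valid check of the primary result. That condition is plausible but not established, and neither the size nor the sign of any bias can be derived from the documents. The 12–29% loss and the 3.5° overstatement are illustrations only. Nothing suggests that the primary ANCOVA is affected, since co-interventions are not named in it. The absence from the Section 3 list is an omission to align. The rule should be corrected, but it does not threaten the trial's main inference.

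**What to change.** - In Section 2.3, remove the covariate rule for values recorded after allocation. Limit covariates in the sensitivity models to pre-randomisation values; a week-2 record made before allocation is acceptable.
- Report co-interventions descriptively by arm, under the ITT strategy already in Section 3, which needs no change for this.
- If the effect in the absence of co-interventions is wanted, state it as a separate estimand, use a method suited to post-randomisation variables, and label it exploratory.
- Make Sections 2.3 and 3 give the same set of sensitivity analyses.

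The cost is protocol wording only. Data collection, sample size and the primary analysis are unchanged. Because the change touches analyses, Section 3.2 may require ethics committee approval as a substantial modification; it is best made before recruitment.
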